# Evaluating the safety and feasibility of a new surgical treatment for forearm fractures in older children: study protocol for a randomised controlled trial

**DOI:** 10.1186/s13063-019-3458-5

**Published:** 2019-06-03

**Keywords:** Forearm fractures, Elastic stable intramedullary nailing, Hybrid fixation, Randomised controlled trial

## Abstract

**Background:**

Both-bone forearm fractures are a common fracture, accounting for 3.4% of all paediatric fractures. For now, elastic stable intramedullary nailing (ESIN) and open reduction and internal fixation (ORIF) are the common surgical procedures for paediatric both-bone forearm fractures. Both ORIF and ESIN have their shortcomings. Therefore, we need to find another surgical treatment which can decrease the rate of complications and improve the clinical efficacy. Our study plans to test hybrid fixation, using an ESIN fixation for the radius and an ORIF for the ulna. Our study will conduct a randomised controlled trial (RCT) comparing double plate fixation with hybrid fixation for treatment of both-bone forearm fractures in older children between 10 and 16 years of age. The objectives of this trial are to compare the effectiveness between double plate fixation and hybrid fixation for treatment of both-bone forearm fractures in older children.

**Methods:**

An RCT will be conducted, and the participants included will be randomly divided into either the hybrid fixation group or the double plate fixation group, at a ratio of 1:1. The primary clinical outcome measures are the Disabilities of the Arm, Shoulder and Hand score and radiological evaluation. Secondary clinical outcome measures are intraoperative blood loss, surgical duration, visual analogue scale score after surgery, hospital duration after surgery and complications. Follow-up will be conducted at 2 weeks and 1, 3, 6 and 12 months postoperatively.

**Discussion:**

The trial will provide a new surgical treatment for forearm fractures in older children. Our hypothesis is that there is no clinically relevant difference in the primary outcome measures between the two treatment groups.

**Trial registration:**

Chinese Clinical Trial Registry, ChiCTR1800018060. Registered on 26 August 2018.

**Electronic supplementary material:**

The online version of this article (10.1186/s13063-019-3458-5) contains supplementary material, which is available to authorized users.

## Background

Both-bone forearm fractures are a common fracture, accounting for 3.4% of all paediatric fractures and 26% of paediatric upper extremity fractures [1, 2]. For children under 10 years old, most both-bone forearm fractures can be treated successfully with casting due to the considerable bone remodelling potential [3–5]. Although closed reduction and casting is a feasible choice for children older than 10 years old [6], there are adverse outcomes of conservative treatment, such as nonunion of the fracture, malunion and secondary surgery [7]. Also, the standard of amount of angulation or malrotation is not clear in this age group. In addition, for open fractures, fractures associated with compartment syndromes, elbow injuries, combined injuries such as Monteggia fractures and Monteggia equivalents, significant comminution or further displacement with nonoperative treatment, operative treatment is required [8–10]. For now, elastic stable intramedullary nailing (ESIN) and plate screw fixation are the common surgical procedures for paediatric both-bone forearm fractures [11]. The advantages of ESIN fixation for paediatric both-bone forearm fractures compared with plate fixation include less wound infection, shorter operative time, smaller edge, less soft tissue dissection, ease of implant removal and early return to activity after implant removal [12–16]. However, ESIN fixation also has its own shortcomings, including delayed union and nonunion, refracture, implant migration or failure and compartment syndrome [17–21]. Compared with younger children, the rate of complications is obviously increased in those over 10 years old [22–24]. Open reduction and internal fixation (ORIF) is a surgical alternative in this age group and offers some potential benefits, including immediate fracture stabilisation and anatomic reduction, which are important for restoring forearm rotation [25, 26]. However, ORIF has been criticised because of its longer operation time, the amount of soft tissue dissection and periosteal stripping, the increased amount of bleeding and the increased risk of wound infection [27, 28].

Both ORIF and ESIN fixation have their shortcomings. Therefore, we need to find another surgical treatment which can decrease the rate of complications and improve the clinical efficacy. Our study plans to test hybrid fixation, using an ESIN fixation for the radius, and open reduction and plate screw fixation for the ulna. Compared with double plate fixation, hybrid fixation not only reduces soft tissue dissection and potentially refracture rates after implant removal, but it also incorporates some advantages of ESIN fixation. Feng et al. conducted a case-control study and found that mixed fixation was a feasible method [29]. Our study will conduct a randomised controlled trial (RCT) comparing double plate fixation with hybrid fixation for treatment of both-bone forearm fractures in older children between 10 and 16 years of age.

The objectives of this trial are to compare the effectiveness between double plate fixation and hybrid fixation for treatment of both-bone forearm fractures in older children. Our hypothesis is that there is no clinically relevant difference in the primary outcome measures between the two treatment groups.

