### Sample size

The sample size calculation is performed using G*Power 3.1 [30] and is based on Disabilities of the Arm, Shoulder and Hand (DASH) score as the primary outcome measure in this trial. For the sample size calculation, we used an α level of 0.05 and a β level of 0.1. We assumed the minimal clinically important difference (MCID) of the DASH to be 5 points, with the standard deviation (SD) being 14.7 [31]. Using these assumptions, the required sample size is 98 per group with 90% power to show a clinically important difference between the treatment methods with a two-sided type I error rate of 5%. With an assumption of 12.5% lost to follow-up, we decided to include 112 participants per group.

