### Statistical analysis

The trial data will be analysed using SPSS for Windows software (V.19.0; SPSS, Chicago, IL, USA). For continuous variables, the Shapiro-Wilk test will be applied to determine if they follow a normal distribution. For normally distributed variables, the means will be calculated and compared using the independent samples *t* test (Student’s *t* test) or analysis of variance (ANOVA); otherwise, the Mann-Whitney *U* test will be used for group comparisons. The χ2 test will be used to analyse qualitative variables. In all analyses, *p* < 0.05 will be taken to indicate statistical significance.

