### Expectations

Our expectation is that there will be no clinically relevant difference in the primary outcome measure between the two treatment groups. Hybrid fixation will be another effective option for treatment of both-bone forearm fractures in older children.

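### The protocol expects to conclude that there is no clinically relevant difference, but its sample size and tests address only whether a difference exists, so it gives no valid route to that conclusion

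*Protocol article*

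**What the plan says.** The hypothesis appears in the abstract and again at the end of the Background section: "Our hypothesis is that there is no clinically relevant difference in the primary outcome measures between the two treatment groups". The Expectations section in the Discussion repeats it, "Our expectation is that there will be no clinically relevant difference in the primary outcome measure between the two treatment groups", and follows it directly with the favourable conclusion: "Hybrid fixation will be another effective option for treatment of both-bone forearm fractures in older children".

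The design is stated in different terms. The Sample size section takes a DASH difference of 5 points (the assumed MCID), an SD of 14.7 and a two-sided 5% error, and reports that "the required sample size is 98 per group with 90% power to show a clinically important difference between the treatment methods". Allowing for 12.5% loss gives 112 per group.

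The Statistical analysis section plans a t test or ANOVA for normally distributed variables, the Mann-Whitney U test otherwise, and the chi-square test for qualitative variables. Its one criterion for all analyses is that p < 0.05 "will be taken to indicate statistical significance".

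The Primary outcome measures section names the DASH score, with 12 months as the primary time point, and radiological evaluation of nonunion and malunion.

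**The concern.** The hypothesis is about the absence of a relevant difference, while the sample size and the tests are about its presence. A test of no difference can count against the hypothesis by finding a difference, but it cannot confirm it. The 5-point MCID enters only as the difference to detect, never as a limit that the observed data must rule out.

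What is at stake is the trial's main conclusion, that hybrid fixation is an acceptable alternative to double plating in children aged 10 to 16. If the 12-month DASH comparison is non-significant, the protocol has no rule that separates a result excluding a 5-point disadvantage from one that is too imprecise to say. The noisier the data, the more likely a non-significant result becomes, although noise is no evidence of similarity.

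**Working it through.** **Inputs (Sample size section):** difference 5 points, SD 14.7, two-sided alpha 0.05, power 90%, 98 evaluable per group. **Assumptions for this check:** limits of -5 and +5, taken from the protocol's MCID because it states no margin; normally distributed differences in means; normal quantiles unless t is stated.

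**1. The protocol's own figure.**
- n per group = 2 × [SD × (1.960 + 1.282) / difference]² = 2 × [14.7 × 3.242 / 5]² ≈ 182, or 183 with the t distribution. The stated 98 is not reproduced.
- At 98 per group the power is about 66%.
- The step for losses does reproduce: 98 / (1 − 0.125) = 112.
- To give about 98, the SD would have to be about 10.8 at a 5-point difference, or the difference about 6.8 points at SD 14.7.

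**2. Precision at 98 per group, SD 14.7.**
- SE = 14.7 × √(2/98) = 2.10.
- 95% CI half-width = 1.972 × 2.10 = 4.14 (t, 194 degrees of freedom), or 4.12 with 1.960.
- A just non-significant result has an estimate of about 4.1, so its far CI limit is about 2 × 4.1 = 8.2 points, beyond the MCID.

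**3. How often a non-significant result would mislead or be uninformative.**
- True difference 5: 5 / 2.10 = 2.381, and 2.381 − 1.960 = 0.421. P(significant) ≈ Φ(0.421) = 0.663, so P(non-significant) ≈ 0.337 (0.341 with the t distribution).
- True difference 0: P(95% CI wholly within ±5) ≈ 2 × 0.663 − 1 = 0.326 (0.318 by simulation with the t distribution). With a 90% CI: 2 × Φ(2.381 − 1.645) − 1 = 0.538 (0.534 by simulation).
- True difference 0: P(non-significant but 95% CI reaches 5 on one side) ≈ 0.950 − 0.326 = 0.624.

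**4. How much of this belongs to the sample-size error.**
- With 183 per group at SD 14.7, SE = 14.7 × √(2/183) = 1.54. Non-significance at a true 5 falls to about 10%. The 95% CI lies within ±5 in about 2 × Φ(5/1.537 − 1.960) − 1 ≈ 0.80 of trials when the true difference is zero.
- With 98 per group but an SD of 10.7, SE = 1.53 and the same probability is about 0.81.
- The 34% and 32% therefore largely reflect the unsupported 98 per group. The mismatch between hypothesis and tests remains at any sample size.

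**5. No losses (112 per group, SD 14.7).** The SE is 1.96 and the half-width about 3.9. Non-significance at a true 5 is about 28%, and the 95% CI lies within ±5 about 44% of the time at a true difference of zero.

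**The case against.** Four points can be made for the protocol.

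*The aim is ambiguous.* The stated objective is only to compare effectiveness, and the Background motivates the trial by a search for fewer complications and better efficacy, which is superiority language. The hypothesis could be a loosely worded null hypothesis, which would fit the sample size. This stands in part. The qualifier about clinical relevance and the Expectations section, which treats the absence of a difference as the favourable result, weigh against it. It is still a good reason to let the sponsor choose the framing.

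*Nothing says that p >= 0.05 will be taken as proof of similarity.* This stands. A reader might infer such a rule from the hypothesis, the tests and the Expectations section together, but no sentence states it, and Expectations is discussion text, not a decision rule. What the text supports is that no valid route to the expected conclusion is given.

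*The trial could still answer the question.* This stands too. A reader might conclude that it cannot, but a half-width of 4.1 is below 5, so the CI can exclude a 5-point difference in either direction when the estimate lies within about 0.9 points of zero (5 − 4.14 = 0.86).

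*A CI rule may sit in an analysis plan that is not shown.* It may, and its absence from a condensed article would be no finding by itself. The point rests on elements that the article does state and that do not fit together: the hypothesis, the basis of the sample size, the tests and the significance criterion.

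**Conclusion.** The point holds as a mismatch within the protocol. The hypothesis and expected conclusion are that no relevant difference exists, yet the sample size and every planned test ask only whether a difference exists. As written, the plan gives no valid route to the conclusion that it expects.

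At the protocol's SD and 98 evaluable per group, a non-significant DASH result is compatible with a difference of up to about 8 points. If the truth were the full 5 points, the test would miss it about one time in three. These sizes rest on SD 14.7 and should not be charged to the mismatch alone, since much of the imprecision comes from 98 per group not following from the stated inputs. The choice of ±5 is an assumption drawn from the MCID, but the mismatch does not depend on it.

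**What to change.** No change to enrolment is needed. Before analysis, the sponsor should adopt one of two courses.

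**(a) Keep the similarity aim and give it a rule.** The primary conclusion rests on the hybrid-minus-plate difference in mean 12-month DASH with a two-sided 95% CI, whatever the normality test shows, because the Mann-Whitney branch yields no mean difference to set against 5 points. The absence of a clinically relevant difference is concluded only if the whole CI lies within -5 to +5; otherwise the result is inconclusive on that question. The chance of success at 98 per group is reported: about 32% at SD 14.7 if the true difference is zero, and about 80% if the SD is nearer 10.7.

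**(b) Restate the hypothesis as a difference question** and remove the similarity expectation from the abstract, Background and Expectations sections.

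Under either course, state that p >= 0.05 alone supports no claim of similarity, and apply the same restriction to nonunion and malunion, since the hypothesis covers the primary outcomes in the plural.

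The cost is wording and one confidence interval. The real downside under (a) is a lower stated chance of a positive conclusion. For 90% power to show equivalence at SD 14.7 and a true difference of zero, the trial would need about 188 evaluable per group with a 90% CI (2 × [14.7 × (1.645 + 1.645) / 5]²) or about 225 with a 95% CI (2 × [14.7 × (1.960 + 1.645) / 5]²). The figure of 98 per group should be corrected or explained as a separate matter.

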## Methods

### Study setting

The study, based on an RCT, will be conducted in our hospital. The trial was approved and monitored by the Ethics Research Committee of our hospital, and it conforms to the Declaration of Helsinki Ethical Principles for Medical Research Involving Human Subjects. This trial has been registered at the Chinese Clinical Trial Registry (ChiCTR1800018060). The protocol conforms to the Standard Protocol Items: Recommendations for Interventional Trials (SPIRIT) guidelines (see Additional file 1). Figure 1 shows a flow chart of the trial design.

**Fig. 1 Fig1:**
[figure not shown]
Flow chart of the trial

### Consent

Informed consent takes place in a face-to-face setting at the research site. Patients’ parents will have at least 24 h to consider participation and will be encouraged to discuss the study with their family and other healthcare professionals. A full verbal explanation of the study, a written Patient Information Sheet (detailing rationale, design and personal implications of trial entry) and informed consent form will be provided. Participants may withdraw at any stage of the trial. Consent will be obtained prior to collection of baseline assessment data and subsequent randomisation.

### Participants

Some members of our group will assess patients with both-bone forearm fractures for eligibility. The diagnosis will be verified using anteroposterior and laterolateral radiographs. All eligible patients’ parents will be introduced to the study, given detailed written information about it and then asked to participate and to sign the written informed consent form. Inclusion and exclusion criteria are listed as follows.

#### Inclusion criteria

The inclusion criteria are as follows:Boys or girls aged 10–16 years oldOnly unilateral displaced closed both-bone forearm fracturesAO fracture classification types 22-A3 and 22-B3Fracture has been present for less than 10 daysThe time from injury to operation is less than 14 daysParents have signed informed consent form and are willing to participate in all follow-up visits.

#### Exclusion criteria

The exclusion criteria are:Bilateral fracture, open fractures, complex forearm fractures (Monteggia fractures, Galeazzi fractures, intra-articular elbow or wrist fractures) and pathologic fracturesHistory of trauma of the same upper extremity causing functional deficitDisease that significantly affects the general condition of the patientSignificantly impaired ability to cooperate for any reason (substance abuse, mental disorder, dementia)Unwilling to accept both treatment methods.

### Participant withdrawal criteria

Patients will be withdrawn for the trial for the following reasons:Patients request to withdraw from the trialOccurrence of a serious adverse eventOccurrence of factors making it difficult to sustain the process or investigator’s decision to terminate because of clinical trial results affected by some factorsPatient death or patient lost to follow-up.

### Participant timeline

A flow chart of the trial is presented in Fig. 1. The time schedule of enrolment, interventions, assessments and visits is shown in Fig. 2.

**Fig. 2 Fig2:**
[figure not shown]
Schedule of enrolment, interventions and assessments

### Sample size

The sample size calculation is performed using G*Power 3.1 [30] and is based on Disabilities of the Arm, Shoulder and Hand (DASH) score as the primary outcome measure in this trial. For the sample size calculation, we used an α level of 0.05 and a β level of 0.1. We assumed the minimal clinically important difference (MCID) of the DASH to be 5 points, with the standard deviation (SD) being 14.7 [31]. Using these assumptions, the required sample size is 98 per group with 90% power to show a clinically important difference between the treatment methods with a two-sided type I error rate of 5%. With an assumption of 12.5% lost to follow-up, we decided to include 112 participants per group.

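### On the protocol's own inputs, 98 per group gives about 66% power, not the stated 90%; 90% would need 183 per group

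*Protocol article*

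**What the plan says.** The Sample size section says the calculation "is based on Disabilities of the Arm, Shoulder and Hand (DASH) score as the primary outcome measure in this trial" and was done in G*Power 3.1. It prints every input:

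- Error rates: "we used an α level of 0.05 and a β level of 0.1", and later in the same section "with a two-sided type I error rate of 5"%.
- Effect and spread: "We assumed the minimal clinically important difference (MCID) of the DASH to be 5 points, with the standard deviation (SD) being 14.7".
- Result: "the required sample size is 98 per group with 90% power to show a clinically important difference between the treatment methods".
- Allowance for 12.5% loss: "we decided to include 112 participants per group".

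The Allocation and randomisation section describes two parallel groups randomised 1:1, 224 patients in all. The Statistical analysis section plans an independent-samples t test (or ANOVA) for normally distributed variables and a Mann-Whitney U test otherwise. Under Primary outcome measures, the primary time point for DASH is 12 months.

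**The concern.** A 5-point difference with an SD of 14.7 is a standardised effect of about one third of an SD. For a two-sided two-sample comparison at 90% power, an effect of that size calls for roughly 180 patients per group, so 98 looks far too small.

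This calculation is the stated justification for enrolling 224 children in a surgical trial. If it is wrong, the trial is much less able to detect the difference it calls clinically important than readers are told. The direction of the error matters too. The Background and Expectations sections anticipate no clinically relevant difference, so a non-significant result is likely to be read as support for that view, and a 90% power claim would lend it weight it does not have.

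**Working it through.** **Inputs (Sample size section unless noted).** Difference δ = 5; SD σ = 14.7; two-sided α = 0.05, so z = 1.960; power 0.90, so z = 1.282; two independent groups, 1:1 (Allocation and randomisation). The standardised effect is d = 5/14.7 = 0.340.

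**Attempt to reproduce 98.** Normal approximation, per group:

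n = 2 × (1.960 + 1.282)² × (σ/δ)² = 2 × (1.960 + 1.282)² × (14.7/5)² ≈ 181.6, so 182.

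The exact noncentral-t calculation for two independent means gives 89.9% power at 182 and 90.1% at 183, so 183 per group. The stated 98 is not reproduced.

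**Power at the stated size.** Noncentrality = d × √(n/2) = 0.340 × √49 = 2.38. The normal approximation gives Φ(2.38 − 1.96) = 66.3%; noncentral t gives 65.9%. With all 112 per group retained, noncentral t gives 71.7%.

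**What 98 per group can detect (noncentral t, SD 14.7).** 90% power at a difference of about 6.8 points; 80% at about 5.9 points. Equivalently, 90% power for 5 points would need an SD of about 10.7.

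**Loss allowance.** 98/(1 − 0.125) = 112, so this step is correct in itself. Applied to 183, it gives 183/0.875 = 209.1, so 210 per group, 420 in total.

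**Other readings, evaluable patients per group:**

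| Reading | n per group |
|---|---|
| Two-sided 5%, 80% power | 137 |
| One-sided 5%, 90% power | 149 |
| One-sided 5%, 80% power | 108 |
| Mann-Whitney, two-sided 5%, 90% (183 ÷ 0.955) | about 192 |
| Non-inferiority, margin 5, 90% (one-sided 2.5% / 5%) | 182 / 149 |
| Equivalence (two one-sided tests), margin 5, 90% (2.5% / 5% each) | 225 / 188 |

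None gives 98. Covariate adjustment could bring 183 down to 98 only with a correlation of about √(1 − 98/183) = 0.68; the article states no such adjustment.

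**Possible origins (inference only).** Two routes reach 98:

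- A matched-pairs Wilcoxon signed-rank calculation with d = 0.340, a normal parent (efficiency 3/π) and two-sided 5% gives 89.96% power at 97 and 90.25% at 98. That would mean the wrong test family was selected.
- The correct two-sample t test with an SD of 10.7 gives 89.94% at 97 and 90.23% at 98. That would mean the printed SD is wrong.

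The article does not settle which, if either, occurred.

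**The case against.** The arithmetic is not in dispute; the best counter-argument concerns cause and remedy. An SD of 10.7 differs from the printed 14.7 by one digit and yields exactly 98 with the correct test. The calculation may therefore have been right and the SD misprinted. In that case, restating the power as 66% would put a wrong figure into the protocol. The cited source of the SD is not available here, so the document proves that inputs and output disagree, not which of them is wrong.

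Part of this stands. The signed-rank explanation should not be presented as the only one, the consequences are conditional on the printed SD, and the SD should be checked before the paragraph is rewritten. It does not rescue the paragraph. 14.7 is the only SD the protocol gives, 10.7 appears nowhere in it, and the text says the sample size follows from the stated assumptions. Nor can condensation for a journal explain the gap, since all inputs and the result are printed.

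It is also fair to say that a superiority calculation under a hypothesis of no difference is a separate design question. It explains why the error matters here but adds nothing to the arithmetic finding.

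**Conclusion.** The concern holds. On the printed assumptions (5 points, SD 14.7, two-sided 5%, two independent 1:1 groups, t test), 98 evaluable patients per group give 65.9% power, and 71.7% if all 112 per group are retained. The stated 98 is little more than half of the 183 needed for 90%. The chance of missing a true 5-point difference is about 34% (1 − 0.659), against the 10% stated. Using the Mann-Whitney test does not help.

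The result rests only on figures in the Sample size section and on the design and test stated elsewhere in the article. It would change only if the SD or difference actually used differs from the one printed, and in that case the paragraph would still need correcting.

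**What to change.** First check the SD of 14.7 against its cited source and against the saved G*Power settings (test family, effect size, SD).

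If 14.7 stands, rewrite the paragraph to say that 98 evaluable patients per group give about 66% power to detect 5 points at SD 14.7 with a two-sided 5% t test; that 112 per group with no loss give about 72%; and that 90% power is reached only for differences of about 6.8 points. Delete the statement that 98 per group is the number required for 90% power. If the check shows that a different SD was used, print that SD with its source and show that the calculation reproduces.

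Record the change in the trial registry, which the Protocol amendments section names as the channel for modifications. The cost is one corrected paragraph, a registry update and, if 14.7 stands, a less favourable stated power. No extra patients are needed for the correction. Whether to enlarge the trial, towards 210 per group for 90% power after 12.5% loss, is a separate sponsor decision.
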